**Exclusion criteria**
Older individuals who are currently admitted to a nursing home.Older individuals who are mentally incapacitated based on a history of confirmed mental disorder or unable to understand the research protocol when briefed by the researcher.

### Sample Size Calculation and Sampling Technique

The sample size for the quantitative phase was estimated based on the total population of older people in the study locations, the 95% CI, a precision error of 5%, and estimates from previous related studies on the proportions of participants with satisfactory accessibility and receptiveness levels toward counseling [28]. Specifically, the sample size was estimated by using the formula for analytical and cohort studies presented below:

[figure not shown]

Where

n = sample size

*z*_1–_*_α_*_/2_ = *z* statistic for 95% CI = 1.96

*z*_1-_*_β_* = *z* statistic for 90% power = 1.28

*P*_1_ = Proportion of participants with satisfactory accessibility and receptiveness levels toward counseling in 1 group and

*P*_2_ = Proportion of participants with satisfactory accessibility and receptiveness levels toward counseling in 1 group

*P*_1_ and *P*_2_ were obtained from previous studies reporting the proportions of participants with satisfactory accessibility and receptiveness levels toward counseling [15,28]. The obtained values were substituted into the equation to calculate the required sample size (n). The computed sample size was adjusted for eligibility by assuming that approximately 30% of the participants have access to and are receptive to counseling. Furthermore, a nonresponse rate of 20% was also considered before deciding on the final sample size.

The probability proportionate to size method was used to allocate sample size for each region and part of Singapore to facilitate proportionate distribution of older individuals receiving some form of preventive, primary, or long-term care in the community through VWOs. Thereafter, a simple random sampling technique was used to obtain the required number of participants from each region. Meanwhile, purposive sampling was used in selecting the SACs.

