**Methods:**

A mixed method study design involving quantitative and qualitative methods will be used. Older individuals receiving some form of preventive, primary, or long-term care in the community through voluntary welfare organizations from the senior activity centers located in eastern Singapore participated in the qualitative phase. Six older individuals from each senior activity center have been enrolled for the interview phase to explore 6 components: the Advanced Care Planning (ACP) booklet, Trait Meta Mood Scale (TMMS), accessibility and receptiveness toward counseling, and emotional management and decision-making. The ACP, an instrument designed to assess advanced care planning among older individuals, and the TMMS, an instrument developed to measure meta-mood experience and emotional management, were used in the quantitative phase among 100 participants. The data will be analyzed thematically using NVivo version 12, whereas descriptive statistics and a 2-tailed, 1-sample *t* test will be conducted in SPSS (version 25; IBM Corp) for empirical data analyses.

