## Results

We have obtained ethical approval to conduct this study from the Universiti Sains Malaysia Human Research Ethics Committee (USM/JEPeM/21110760). The qualitative phase, which involved a semistructured interview, was conducted from January 14, 2022, to February 16, 2022, among 25 individuals aged 66-86 years. Thematic analysis of the data is still ongoing. Meanwhile, the quantitative phase commenced on March 22, 2022, with 100 participants providing signed and informed consent to participate in the study. The face-to-face administration of the ACP and TMMS instruments and data collection closed on May 10, 2022. Data analysis and manuscript writing was performed in March 2023.

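### The stated 5% precision at 95% confidence is not delivered by the 100 people surveyed at any proportion between about 7% and 93%, and the article does not show how 100 arose

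*Protocol article*

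**What the plan says.** Under Sample Size Calculation and Sampling Technique, the article bases the quantitative sample size on the older population of the study locations and on "the 95% CI, a precision error of 5%, and estimates from previous related studies on the proportions of participants" with satisfactory access and receptiveness. It continues that "the sample size was estimated by using the formula for analytical and cohort studies presented below". The formula is a figure that is not available here, but its terms are listed: a z "statistic for 95% CI = 1.96", a z "statistic for 90% power = 1.28", and two proportions, P1 and P2. These proportions "were obtained from previous studies reporting the proportions of participants with satisfactory accessibility and receptiveness levels toward counseling". Both carry the same definition and neither has a value.

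The computed size was then adjusted for eligibility by "assuming that approximately 30% of the participants have access to and are receptive to counseling", and a 20% nonresponse rate was also considered. Neither the computed nor the final size is stated.

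The number 100 appears elsewhere. The Abstract says the two instruments "were used in the quantitative phase among 100 participants", and the Results section says "the quantitative phase commenced on March 22, 2022, with 100 participants providing signed and informed consent to participate in the study". The section on the qualitative phase says that the interview sample was 10% of the computed quantitative size. The number interviewed is 20 in the Abstract and 25 in the Results section.

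**The concern.** The 5% is the only precision statement in the article, and 100 is the only survey size. Put together, they do not agree for mid-range proportions. The survey includes multiple-choice items on end-of-life care, the analysis is largely descriptive, and the findings are addressed to policymakers. Someone who carried the 5% over to the reported percentages would think most of them more precise than they are, by a factor of up to about two.

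The section also joins two different ways of sizing a study. A precision calculation needs a proportion and a margin. A power calculation needs two proportions, alpha and power. The text names a margin but lists the terms of the power calculation, so it is not clear what the 5% did.

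**Working it through.** **Inputs.** 95% confidence, z = 1.96; precision 5%, read as absolute percentage points; 100 respondents; 62,750 + 43,700 = 106,450 older residents of Bedok and Tampines (Study Design and Study Area). Simple random sampling is assumed. No planning proportion is given, so a range is shown.

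**1. Half-width with 100 respondents, and number needed for ±5 points.** Half-width = 1.96 × √(p(1−p)/100); n = 1.96² × p(1−p)/0.05².

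| p | Half-width at n = 100 | n for ±5 points |
|---|---|---|
| 0.10 | 5.9 points | 139 |
| 0.20 | 7.8 points | 246 |
| 0.30 | 9.0 points | 323 |
| 0.50 | 9.8 points | 385 |

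The values at 0.70 and 0.90 mirror those at 0.30 and 0.10. For example, at 0.30: 1.96 × √(0.21/100) = 0.0898. The exact interval for 30 out of 100 is 21.2% to 40.0%. The 30% is only an illustration here, because the plan uses it as an eligibility adjustment.

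**2. Where 100 does give ±5 points.** This needs p(1−p) ≤ 100 × (0.05/1.96)² = 0.0651, so p ≤ 0.07 or p ≥ 0.93.

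**3. Finite population.** With 106,450 residents, the number needed at p = 0.30 is 322 and the half-width at n = 100 stays at 9.0 points. The real sampling frame (service users of the selected centers) is smaller and its size is not given. Assumed frames of 1,000, 500 and 200 people give 8.5, 8.0 and 6.4 points. Only a frame of about 145 people gives ±5.

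**4. If 100 were the size after nonresponse.** The analysable number would be 100 × 0.8 = 80, and the half-width at p = 0.30 would be 1.96 × √(0.21/80) = 0.100.

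**5. The size implied by the interview rule.** 20/0.10 = 200 and 25/0.10 = 250. Neither is 100. With 250, the half-width at p = 0.20 would be 1.96 × √(0.16/250) = 0.0496. A larger computed size could therefore have met the 5% at some proportions.

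**6. The formula as listed.** It cannot be reproduced without P1 and P2. Taking P1 = 0.30 for illustration, with two-sided alpha 0.05 and 90% power, P2 = 0.40, 0.50 and 0.60 need 477, 124 and 56 per group before inflation. Fifty per group (100 in total) suffices from about P2 = 0.62. Some pairs of values therefore do give 100.

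**The case against.** The strongest reply is that the article never claims 100 was computed for 5% precision. It gives 100 as the number surveyed, and the interview rule points to a computed size of 200 to 250. The 5% may then have been a correct planning input, with the gap arising at enrollment. This stands. A reader might infer that the stated precision is an arithmetic error of nearly a factor of two, but the documents do not support that. The factor depends on taking 30% as the planning proportion, and the plan applies 30% only after the size was computed.

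Two further inferences also fail. One is that 100 cannot be the output of the formula. With P1 and P2 unreported this cannot be known, and some pairs of values do give 100. The other is that the 30% adjustment is plainly misapplied and should be struck out. The inclusion criteria require willingness to attend counseling sessions, which overlaps with being receptive, so an eligibility adjustment may have a basis. The article does not say how the 30% was applied, so any inflated total built on dividing by 0.3 is an assumption.

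It is also fair to say that the article lists 5% as a basis for sizing and does not promise it as the margin of the reported results. No analysis rule treats small differences as real.

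None of this removes the mismatch. If 100 was the intended size, it does not give the stated precision at mid-range proportions. If it was a shortfall, the stated precision no longer describes the survey. If 5% was meant as alpha, precision is the wrong word for it.

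**Conclusion.** The concern holds in a limited form. The stated basis of 5% precision at 95% confidence is not delivered by 100 respondents for any proportion between about 7% and 93%. For proportions of 30% to 50%, the half-width is about ±9 to ±10 points. This assumes absolute precision, simple random sampling and a sampling frame that is not very small. Because the centers were selected purposively, the figures are likely to be optimistic.

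The documents do not show where the gap arose. The rationale mixes precision and power, the two proportions have no values and no distinct definitions, and no computed size is stated. The point should be corrected, but it is one of reporting and interpretation and does not invalidate the survey.

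**What to change.** In Sample Size Calculation and Sampling Technique:

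- Replace the 5% precision claim with wording such as: *With 100 respondents, the 95% confidence interval for a proportion between 30% and 50% has a half-width of about 9 to 10 percentage points under simple random sampling; the purposive selection of centers probably makes this optimistic.*
- State whether precision or power set the size. Define P1 and P2 separately, give their values and the computed size, and say how 100 arose from it, including any shortfall.
- Explain how the 30% adjustment was applied and why, since its wording is almost the same as that of the outcome being sized.

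In the results, report each survey proportion with its 95% confidence interval.

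The cost is a few sentences and some added intervals in the tables. The stated precision becomes less favorable. No new data or added recruitment is needed.

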A structured questionnaire was also developed to assess participants’ views regarding counseling and its impact on their dignity and decision-making process. This was based on the themes identified in the qualitative study and an in-depth review of several studies in the literature. Operational definitions were also developed based on the themes obtained. Three experts assessed the questionnaire for content validity. Thereafter, the instrument was distributed to 10 social workers or counselors for face validity assessment. The comments received were reviewed and necessary modifications were made. The final questionnaire was presented in English, and no translation into local languages was conducted. Pretesting was performed on 20 older individuals from selected SACs for internal consistency and reliability. Findings from the experts’ opinions and pilot testing were used to prevent potential ceiling and floor effects from the questionnaire items that may affect accurate data interpretation. The developed questionnaire was distributed to randomly selected older individuals at all selected SACs. The data obtained from the quantitative and qualitative approaches were combined to provide a more robust assessment of the study. Table 1 depicts the research matrix.

**Table 1 table1:** Research matrix.

Research objectives	Quantitative	Qualitative
To assess advance care planning among older people and their perception of life and health, end of life, and end-of-life care	✓	✓
To explore older people’s accessibility and receptiveness toward counseling		✓
To elucidate older people’s perspectives on counseling and its impact on emotional management and decision-making		✓
To assess older people’s competencies in emotional management	✓	
To propose an intervention model for enhancing older people’s well-being and dignity through psychological counseling	✓	✓

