### Data Analysis

Findings from the qualitative study will be transcribed and coded. Interview transcripts will be analyzed using NVivo (version 12; QSR International). The identification, coding, and categorization of meaningful patterns into themes and subthemes will be performed to facilitate the construction of a structured questionnaire for the quantitative study. For the quantitative phase, the internal consistency of the questionnaire items will be evaluated using a reliability test based on Cronbach α values. Items will be considered acceptable and reliable if the Cronbach α value is equal to or greater than .7. Participants’ background information and other sections in the questionnaire will be analyzed using descriptive statistics. Continuous variables will be subjected to normality tests using the Smirnov-Kolmogorov test and presented as means (SD) or medians (IQR) accordingly. Statistical tests such as a 2-tailed, 1-sample *t* test or Wilcoxon signed rank test will be applied. A *P* value of .05 will be considered statistically significant, and all empirical analyses will be performed using SPSS (version 25; IBM Corp). The flow of the research process, including the vital concepts, is presented in Figure 1.

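### The sample size rests on a two-proportion, 90%-power formula that fits no described analysis, and on a 5% precision that 100 participants do not deliver

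*Protocol article*

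**What the plan says.** The section Sample Size Calculation and Sampling Technique names two bases for the quantitative phase. The first is a precision basis: a 95% confidence interval with a 5% error. The second is a formula: "Specifically, the sample size was estimated by using the formula for analytical and cohort studies presented below". Its symbol key gives a "statistic for 95% CI = 1.96", a "statistic for 90% power = 1.28", and two proportions. P1 is the "Proportion of participants with satisfactory accessibility and receptiveness levels toward counseling in 1 group and" and P2 has the same definition, word for word. Both "were obtained from previous studies reporting the proportions of participants with satisfactory accessibility and receptiveness levels toward counseling". Adjustments for eligibility (about 30%) and nonresponse (20%) follow. The section prints no resulting number; 100 appears in the Abstract and Results as the number enrolled.

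On the analysis, Data Analysis says: "Statistical tests such as a 2-tailed, 1-sample *t* test or Wilcoxon signed rank test will be applied". The Abstract names descriptive statistics and the one-sample *t* test. Strengths and Limitations calls the design cross-sectional.

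On the endpoint, the Table 1 row "To explore older people’s accessibility and receptiveness toward counseling" is ticked under Qualitative only, and Expected Findings describes that objective as a matter of qualitative analysis. On the quantitative instruments, Results says: "The face-to-face administration of the ACP and TMMS instruments and data collection closed on May 10, 2022".

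**The concern.** A power term together with two proportions belongs to a comparison of two groups. The article defines no two groups, and because P1 and P2 share one definition, the symbol key does not say what would be contrasted. The endpoint that sizes the survey is also the one that Table 1 leaves to the interviews.

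At stake is what a reader may conclude from the survey. Someone who sees 90% power and 5% precision in the sample-size section may credit the 100 responses with properties that were worked out for a different analysis, or that 100 people cannot give. Recruitment is closed, so the remedy is an accurate statement of what the data can support.

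**Working it through.** **1. The plan's own figure.** The z-values are right: 1.960 for a two-sided 5% level and 1.282 for 90% power. The sample size itself cannot be reproduced, because the equation is a figure that is not shown and P1, P2 and the computed number are not in the text. I do not count that against the article. The only other trace of the computed number is in the Qualitative Phase section, which sets the interview sample at 10% of it. With 20 interviewees (Abstract) or 25 (Results), that implies 20/0.10 = 200 or 25/0.10 = 250. Nothing in the text ties the calculation to 100.

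**2. Sizing basis against described analysis.**

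| Item | Sample-size section | Rest of the article |
|---|---|---|
| Groups | Two proportions, P1 and P2 | One cross-sectional sample; no groups defined |
| Test | Implied two-proportion comparison at 90% power | One-sample *t* or Wilcoxon signed rank; descriptive statistics |
| Endpoint | Satisfactory accessibility and receptiveness | Qualitative only (Table 1, Expected Findings) |
| Instruments for the 100 | Not named | Advanced Care Planning (ACP) booklet and TMMS (Abstract, Results), plus a structured questionnaire on views of counseling and its impact on dignity and decision-making |

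The bases differ in every row that can be compared.

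**3. The 5% precision.** I read it as ±5 percentage points, the lenient reading, since 5% of the proportion itself would be stricter. Required number: n = 1.96² × p(1 − p) / 0.05². The values of p are assumptions.

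- p = 0.30: 3.8416 × 0.21 / 0.0025 = 322.7, so 323
- p = 0.50: 3.8416 × 0.25 / 0.0025 = 384.2, so 385

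Dividing by 0.8 for the stated nonresponse gives 404 and 481. A finite-population correction with the 62,750 + 43,700 = 106,450 older residents of Bedok and Tampines changes little (322 and 383 before nonresponse).

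Margin with n = 100: 1.96 × √(p(1 − p)/100).

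- p = 0.30: ±9.0 points
- p = 0.50: ±9.8 points
- p = 0.10: ±5.9 points

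To reach ±5 points with 100 people, p(1 − p) must not exceed 0.0025 × 100 / 3.8416 = 0.065, so p must be below about 7% or above about 93%.

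**4. What 100 gives for the named test.** The 95% margin for a mean is t(0.975, 99 df)/√100 = 1.984/10 = ±0.198 SD. Power of a two-sided 5% one-sample *t* test comes from the noncentral *t* distribution with noncentrality 10d, where d is the shift in SD units:

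| Shift (SD) | Power |
|---|---|
| 0.1 | 17% |
| 0.2 | 51% |
| 0.3 | 84% |
| 0.327 | 90% |
| 0.4 | 98% |

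The article gives no reference value or SD, so these stay in SD units.

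**The case against.** The two-group form is inferred from the symbol list, since the equation is not visible. The inference is strong but remains an inference. The list of tests is introduced as examples, and Strengths and Limitations speaks of associations involving accessibility and receptiveness, so a fuller plan could contain a comparison. This stands: one can say that no two-group comparison is described, not that none will ever be made. The identical definitions of P1 and P2 may be a drafting slip.

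The article also uses 90% only as a formula input and never claims that power for the study. A reader might go further and infer that no planned analysis has 90% power, or that the survey is underpowered. The documents do not support that. Power depends on the effect, the one-sample *t* test does reach 90% at about 0.33 SD, and no target effect is stated to judge it against. Power figures for a split of the 100 into two halves would be equally unsupported, because neither groups nor P1 and P2 are given.

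Finally, a 5% precision basis suits a descriptive survey and might be offered as the real justification. It does not rescue the number, as step 3 shows.

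**Conclusion.** The concern holds in this form: the 90% power in the sample-size section was not derived for any analysis the article describes, and its endpoint is assigned to the qualitative phase. The 5% precision named beside it is missed by the 100 enrolled, with a margin of about ±9.0 to ±9.8 points for proportions of 30% to 50%, where ±5 would take about 323 to 385 people before nonresponse.

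The mismatch rests on the article's own wording. The sizes assume those proportions, simple random sampling and 100 usable responses; the 0.33 SD and ±0.20 SD figures also assume a roughly normal mean.

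A reader might also infer that the structured questionnaire already supplies the missing quantitative endpoint. The article does not describe it as measuring accessibility or receptiveness, so that cannot be taken for granted.

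**What to change.** In Sample Size Calculation and Sampling Technique, remove the two-proportion formula, the 90% power figure and the 5% precision as the justification for 100. All three must go: leaving the 5% in place would contradict the margins that replace it. State instead what 100 participants deliver:

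- about ±9.0 to ±9.8 points (95% CI) for a proportion between 30% and 50%;
- about ±0.20 SD for a TMMS mean;
- 90% power for a shift of about 0.33 SD, if a one-sample *t* test is kept, with its reference value named.

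Then settle the endpoint. If the structured questionnaire was given to the 100 and contains accessibility and receptiveness items, tick Quantitative for that objective in Table 1, align Expected Findings, and report those proportions with 95% CIs. If either condition fails, leave Table 1 as it is and take this endpoint out of the sample-size rationale.

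The cost is a rewritten section, possibly one row of Table 1 with its matching sentence, and a less favourable stated figure. No extra participants are needed.

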## Methods

### Study Design and Study Area

This study uses a mixed method research design by combining quantitative and qualitative approaches to explore the life experiences of Singaporeans older than 60 years and interpret their lived experiences, such as interactions with qualified counselors accredited by the Singapore Association of Counseling and Singapore Association of Social Workers or social workers. Data are gathered using an exploratory sequential mixed methods design, thereby broadening the scope and dimension of the study. Both qualitative and quantitative approaches offer exceptional strengths that will facilitate robust findings in this study [24-26].

The 5 Singaporean estates with a high number of individuals aged 60 years and older [27] were identified. Bedok and Tampines in the eastern part of Singapore have the largest older populations, with 62,750 and 43,700 people, respectively, followed by Hougang in the northeastern part of Singapore with 41,920 older residents and Ang Mo Kio in the northern part of Singapore with 41,390 older residents. Given the high population of older individuals in Bedok and Tampines, older individuals receiving some form of preventive, primary, or long-term care in the community through voluntary welfare organizations (VWOs) have been recruited for this study. Furthermore, a total of 78 senior activity centers (SAC) in Singapore (a VWO with 10 SACs is located in eastern Singapore) were selected for this study.

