### Study Population

The study population comprises individuals aged 65 years and older from various parts of Singapore.

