### Quality Control Measures

A number of methodological resources, such as mixed method study design, inclusion criteria, and random sampling, were used in this study to minimize bias and ensure quality data collection. The interview session was performed by the principal researcher, while trained enumerators assisted in the quantitative phase of data collection. The enumerators were trained during the pilot test to familiarize them with the research instrument. To further ensure quality control, the principal researcher assessed the enumerators periodically to see if they were following the survey protocol. If necessary, the enumerators also assisted the participants while they completed the questionnaire to minimize missing data. Quality control was assessed in the retrieved questionnaires based on the quality and completeness of the data.

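### The protocol describes incompatible sampling frames, and purposive choice of centers limits inference to clients of the selected senior activity centers

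*Protocol article*

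**What the plan says.** Two descriptions of the sample stand in the protocol article.

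**A national probability sample.** Sample Size Calculation and Sampling Technique states: "The probability proportionate to size method was used to allocate sample size for each region and part of Singapore". It adds that "a simple random sampling technique was used to obtain the required number of participants from each region". Study Population agrees: "The study population comprises individuals aged 65 years and older from various parts of Singapore". The qualitative-phase section also places the SACs in different parts of the country.

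**A local sample reached through chosen centers.** Study Design and Study Area gives the reason for the place of recruitment: "Given the high population of older individuals in Bedok and Tampines, older individuals receiving some form of preventive, primary, or long-term care" were recruited. Both estates are described there as eastern. The next sentence counts 78 SACs in Singapore as selected, but carries the parenthesis "a VWO with 10 SACs is located in eastern Singapore". The sampling section then says "purposive sampling was used in selecting the SACs". The section on instrument development and administration says the questionnaire went to people chosen at random at the selected SACs. The Abstract places the SACs of the qualitative phase in eastern Singapore.

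Quality Control Measures relies on the sampling: "inclusion criteria, and random sampling, were used in this study to minimize bias and ensure quality data collection". The Abstract's Conclusions and the Implications section address older people in Singapore and the country's policymakers.

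**The concern.** The two descriptions license different conclusions. Proportionate allocation over all regions, with simple random sampling in each, would give a sample whose results estimate quantities for the country's eligible older people. Random selection of clients inside purposively chosen centers does not do that. If the national description stays in print, readers will take means, medians and one-sample P values from 100 participants as statements about older Singaporeans. Policymakers, whom the article names as its audience, may then act on results that describe only the clients of certain centers. The limitations section does not warn them: it mentions neither the region nor how the centers were chosen.

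**Working it through.** There is no plan figure to reproduce. The check sets the statements side by side and asks what inclusion probability each implies.

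1. **What the region-wide claim implies.** Let region h hold N_h eligible people, with N in all and a total sample of n. Proportionate allocation gives n_h = n × N_h / N. Simple random sampling within the region then gives each person probability n_h / N_h = n / N. Everyone in every region has the same known chance.

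2. **What the described recruitment implies.** The questionnaire reached people only at selected SACs. A client's probability is therefore Pr(SAC selected) × Pr(client selected, given the SAC). Random selection fixes the second factor. Purposive selection leaves the first unknown, so the product is unknown. A person who is not a client of a selected SAC has probability 0. This contradicts step 1, in whatever order the selections were made.

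3. **Does the ambiguous sentence on centers matter?** It has two readings.
   - *78 SACs selected across Singapore.* This fits the phrase about various parts of the country, but not the reason given for recruiting in Bedok and Tampines. The centers are still said to be purposively chosen, and people outside them still cannot enter.
   - *The 10 SACs of one voluntary welfare organization (VWO) in the east.* This fits Bedok and Tampines, but not allocation to every region.

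   Under both readings step 2 holds, so inference reaches at most the clients of the selected SACs.

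4. **Can the interviews settle the number of SACs?** The Abstract gives six interviewees per SAC. The Abstract reports 20 interviewees and the Results section 25. Then 20 / 6 = 3.3 and 25 / 6 = 4.2, so about 3 to 4 SACs in the qualitative phase. This says nothing firm about the survey.

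5. **Which results are affected.** Data Analysis plans means (SD) or medians (IQR) and a one-sample t test or Wilcoxon signed rank test. The P values presume a random sample from the population about which the conclusion is drawn. Here that population is the clients of the selected SACs.

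6. **Size.** Let W be the share of the target population who are clients of the selected SACs. The bias of a mean for the whole target population is (1 − W) × (mean among those clients − mean among everyone else). The document gives neither W nor the difference, so no value follows. The expression does not contain n, so more participants would not reduce it.

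**The case against.** **Purposive centers with random clients is a common and coherent design.** That stands. It is not an error in itself, and random selection inside a center does guard against hand-picking clients. The fault lies in describing it also as a region-wide probability sample and drawing conclusions to match.

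**The limitations section already concedes narrow generalizability.** It does so in part: it mentions participants with similar characteristics and exclusions through eligibility. It names neither the purposive choice of centers nor a regional restriction.

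A reader might infer more than the document supports:

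- *The sample comes from one provider, at most 10 of 78 SACs (10 / 78 = 13%).* This is a plausible reading of one ambiguous sentence. Read literally, that sentence says 78 were selected, and the article elsewhere speaks of VWOs in the plural. The Abstract's reference to the east concerns the qualitative phase only.
- *Confidence intervals will be misinterpreted.* Data Analysis plans none. The 95% CI appears only as an input to the sample size.
- *The resident counts measure the misallocation.* Bedok and Tampines hold 62,750 + 43,700 = 106,450 of the 189,760 residents in the four estates with counts, or 56%. But these counts serve to identify estates. The stated allocation concerns older people receiving care through VWOs. The text also refers to "The 5 Singaporean estates with a high number of individuals aged 60 years and older" while giving counts for four, so the denominator is incomplete.
- *The allocation used the wrong age group.* The counts are for age 60 and over and eligibility starts at 65, but nothing says that the counts were used for allocation.
- *The region-wide wording is false and should simply be deleted.* The document does not show which description is true. If the survey did reach beyond the east, outright deletion would introduce an error.

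**Conclusion.** The concern holds as a contradiction in the stated sampling design with a definite consequence for inference. The article claims proportionate allocation and random sampling over every region, while its account of centers and questionnaire distribution describes something else. Its results support conclusions at most about clients of the selected SACs.

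This rests on two statements taken at face value: that the SACs were chosen purposively, and that random selection took place at the selected SACs. It does not depend on how many SACs or operators took part, or on whether all were in the east. The size of any bias is unknown. The point should be corrected before results are reported, because it determines the population to which they apply. It does not call for new data.

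**What to change.** - Reconcile the Abstract, Study Design and Study Area, Study Population, the sampling section and the qualitative-phase section into the one design actually used. Give the number, location and operator or operators of the SACs for each phase.
- Keep the region-wide proportionate-to-size statement only if the allocation by region can be shown. Otherwise remove it.
- Describe the sample as purposively chosen SACs with random selection, within them, of eligible clients aged 65 and over.
- In Quality Control Measures, say that random sampling protects against selection of clients within centers, not against selection of centers.
- Limit the Abstract's Conclusions and the Implications section to clients of the sampled SACs.
- Add the purposive choice of centers, and any regional restriction, to Strengths and Limitations.

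The cost is wording and a narrower conclusion. Data collection closed on May 10, 2022, and nothing has to be collected again.
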